**Conclusions:**

If found effective in reducing the patient’s sensitivity long term, these agents can be considered as a treatment choice, and the findings will contribute to the development of a treatment protocol for teeth with sensitivity due to MIH.

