Recently, a new bioactive technology called surface prereacted glass-ionomer (S-PRG) has been tested on many types of dental materials. It is based on a prereacted fluorosilicate particle with polyacrylic acid, allowing the material to have both biological effects from the glass ionomer cement (fluoride release and recharge) [21-23] and the excellent physical, mechanical, and optical properties of nanohybrid composites. The material also has several other ions in its structure, such as aluminum [24], which is related to sensitivity control. Among materials containing S-PRG, a light-cured bioactive coating resin, the PRG Barrier Coat, can provide immediate and long-term relief for up to 6 months [25].

Because new alternatives for the treatment of tooth sensitivity due to MIH are needed, this randomized clinical trial with parallel arms aims to compare three treatment interventions (5% NaF, 4% TiF_4_, and a light-curing S-PRG–based bioactive coating resin). If these agents contribute to the reduction of patients’ sensitivity, they will be considered a treatment choice. The findings of this study will help inform the development of a treatment protocol for teeth with sensitivity due to MIH.

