### Selection of Participants and Sample Size Calculation

The study participants will be selected from the city of Bauru, São Paulo, Brazil, which has a population of 371,690 inhabitants and a Human Development Index of 0.801. Participants aged 6-10 years will be selected from an epidemiological survey in municipal schools. These schools are located in an urban area, in different zones (north, south, east, and west), and will be selected by a draw according to each zone. In the selected schools, all children aged 6-10 years will be evaluated. Children with potential for inclusion in the research will be referred for a clinical examination at the pediatric dentistry clinic of Bauru School of Dentistry, University of São Paulo, and those that have at least one first permanent molar affected by MIH with hypersensitivity complaint and without loss of structure will be invited to participate. The sensitivity complaint will be confirmed by applying a 1-second air jet at a distance of 1 centimeter from the occlusal surface of the tooth; a score of 2 or 3 on the Schiff Cold Air Sensitivity Scale (SCASS) will be considered as a positive result. Patients with orthodontic appliances, syndromes that involve enamel malformation, or behavioral problems during the clinical examination will be excluded. 

The sample size was calculated considering analysis of variance, performed in SigmaPlot (version 12.3; SPSS Inc), and it was considered a minimally detectable difference of 1 on the SCASS scores between groups. A standard deviation of 0.9 was used based on a previous study [28], α error was 5%, β error was 20%, and a dropout rate of 18% was used, which resulted in a total of 60 children (20 per group). The first 60 children who meet the inclusion criteria will be selected to be part of the study, while others who also present with sensitivity but cannot be included will receive the necessary treatment.

Recruitment will take place from October 2019 to December 2021. After allocation and treatment for 4 weeks, the patients will be followed up for 6 months.

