### Treatment Protocol

All children will receive instructions on noncariogenic diet and oral hygiene. Furthermore, the participants will receive an oral hygiene kit with toothbrush and fluoride toothpaste (both Colgate-Palmolive Company). Immediately before treatment, a supervised toothbrushing will be performed with a fluoride-free toothpaste to standardize the treatment phase and to follow the instructions of the S-PRG resin manufacturer. The study risks for participants are minimal and related to the sensitivity due to MIH.

In the control and experimental I groups, the fluoride varnishes will be applied once per week for 4 consecutive weeks. For the experimental II group, the product will be applied the first week and the application will be simulated the following 3 weeks for patient blinding.

All children in the control and experimental I groups will be treated according to the same protocol:

Supervised toothbrushing with fluoride-free toothpaste.Cotton roll isolation of the area.Drying of the tooth using sterile gauze.Varnish application with microbrush according to the manufacturer’s instructions.Instruction of the patient not to eat or drink for 30 minutes and not to brush for at least four hours after application.Reapplication once per week for 3 weeks, following the described protocol.Follow-up.

For the experimental II group, the treatment protocol according to the manufacturer is as follows:

Supervised toothbrushing with fluoride-free toothpaste.Cotton roll isolation of the area.Drying of the tooth using sterile gauze.Material handling within 2 minutes after mixing.Application of a thin layer with the device provided by the manufacturer, then a 3-second wait.Light curing for 10 seconds.Instruct the patient to avoid colored drinks and food for 3 days.Application simulation the following 3 weeks (repeat steps 1-3).Follow-up.

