### Primary Outcome: Treatment Effectiveness

A single trained, calibrated, and blinded examiner (not involved in the treatment application) will assess the sensitivity effectiveness of treatment in all groups at different moments: (1) before the application of each material, (2) immediately after application or simulation, (3) one month after the last application/simulation, (4) two months after the last application/simulation, (5) four months after the last application/simulation, and (6) six months after the last application/simulation. For all evaluations, the WBFPS, SCASS, and FLACC scale will be used as previously described.

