### Follow-up Examinations

Patients will be assessed regarding sensitivity 1, 2, 4, and 6 months after the treatment and will receive preventive instructions concerning diet and biofilm control. At the follow-up appointments, if a tooth displays posteruptive breakdown restricted to enamel, the patient will be kept in the study, but if the breakdown affects dentin (or in the case of a cavitated carious lesion), the patient will receive restorative treatment and be excluded from the study. If the patient has relapsed sensitivity, the initial treatment protocol will be maintained according to each group.

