### Data Analysis

Statistical analysis will be performed with SigmaPlot (version 12.3; SPSS Inc). For the WBFPS, SCASS, and FLACC scale, the three groups and evaluation time will be compared by 2-way repeated measures analysis of variance followed by a Tukey test, based on the recommendation of Cohen [31], to allow for interaction analysis between study factors and to avoid an inflated α error. A Spearman correlation test will be performed to determine if there is a significant correlation among the WBFPS, SCASS, and FLACC scale. The significance level will be set at 5%. Poisson regression will be used to assess the influence of IPV, GI, and discomfort on the outcome. The satisfaction of parents/guardians and participants will be analyzed descriptively.

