## Discussion

MIH presents with various severity levels and side effects, and a broad spectrum of treatment approaches are available [32]. In some cases, hypersensitivity may be present even when there is no enamel loss and no clinically detectable exposed dentin [1,4], and treatment is not always successful with regard to symptomatology. Currently, there is no consensus on the best treatment for teeth with sensitivity due to MIH. Studies focusing on new therapies to treat this condition should be conducted to guide dentists in the selection of patient-friendly procedures, facilitating restorative treatment.

Although only a few clinical studies have evaluated it, the commercially available 5% NaF varnish is considered the gold standard due to its effectiveness and easy application. However, the TiF_4_ varnish, which is not yet available, has a similar application protocol; depending on the results of this study, it could be made available in the market and distributed to treat sensitivity in the future. Although more expensive, PRG Barrier Coat has the advantage of requiring a single application, with reapplication considered based on the patient’s clinical demand. This clinical trial will evaluate as the primary outcome the efficacy of different materials in decreasing sensitivity in teeth affected by MIH.

In this study, sensitivity will be assessed with 3 instruments. Quantifying sensitivity is not easy, especially in children, since responses to stimuli depend on the individual [4], and this limitation should be considered when interpreting the results. The face scale (WBFPS) has been shown to allow children to respond very subjectively. This scale consists of 6 faces, with the first showing a very happy face and the last showing a very sad face [33]. Children may associate the faces with their emotional state and not with their perception of pain. In this study, the SCASS and FLACC scale will be used concomitantly since both include parameters considered indicative of pain that can be detected and classified by an observer.

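### If relapsed children are re-treated and kept in, as the relapse rule most naturally reads, the 2-, 4- and 6-month means compare treat-and-re-treat strategies and do not alone show whether one course lasts

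*Protocol article*

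**What the plan says.** **Relapse rule.** Under Follow-up Examinations: "If the patient has relapsed sensitivity, the initial treatment protocol will be maintained according to each group". The same paragraph removes a child only for breakdown into dentin or a cavitated carious lesion. Relapse is not a reason to leave.

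**Initial course.** Under Treatment Protocol, both varnish arms receive four weekly sessions. For the resin arm, "the product will be applied the first week and the application will be simulated the following 3 weeks for patient blinding". Follow-up begins only after these four weeks.

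**Outcome and analysis.** Sensitivity on three scales is the primary outcome. It is scored "before the application of each material", immediately after, and at 1, 2, 4 and 6 months counted from the last application or simulation. Under Data Analysis, "the three groups and evaluation time will be compared by 2-way repeated measures analysis of variance", followed by Tukey comparisons. The text states no handling of scores taken after a repeat treatment.

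**Durability.** The Abstract's Conclusions make the recommendation depend on reducing the patient's "sensitivity long term, these agents can be considered as a treatment choice". The Introduction cites evidence that the resin "can provide immediate and long-term relief for up to 6 months". The Discussion says: "PRG Barrier Coat has the advantage of requiring a single application, with reapplication considered based on the patient’s clinical demand".

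**The concern.** A rule that acts on relapse, when relapse is itself the primary outcome, gives more product to the arm whose effect wears off sooner. If the extra product works, that arm's later means move towards those of a more durable arm. The ANOVA as stated would pool the first-course and post-re-treatment scores of each arm at each visit.

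The stake is interpretation. Similar 6-month means could arise because both products last, or because one lasts and the other was topped up. The article's conclusion about long-term effect, and its interest in a resin that needs only one application, call for telling these apart.

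**Working it through.** **1. Which reading of the rule?** Four pieces of text bear on it.
- The course in Treatment Protocol is complete before the first follow-up visit. A finished course cannot be continued, so an instruction triggered by relapse most naturally means repeating it.
- Relapse is not listed among the exclusions, so the child stays in.
- The Discussion mentions reapplication on demand, but only for the resin and not as a trial rule. It gives weak support and none for the varnishes.
- The word is *maintained*, not *repeated*. It could mean only that the child is not switched to another product.

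Re-treatment is the more natural reading, but it is not certain.

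**2. Which visits can be affected?** Month 1 is the first follow-up at which relapse can be found. Each first relapse shows undiluted at the visit that detects it (month 1, 2, 4 or 6). Only visits after a re-treatment, at months 2, 4 and 6, can be diluted.

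**3. Time since last product.** Assumptions: month = 30.44 days; weekly sessions on days 0, 7, 14 and 21; visits stay on the calendar fixed from the week-4 session; re-treatment starts at the visit that detects relapse.

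| Score | Varnish | Resin |
|---|---|---|
| Month 6, no re-treatment | 6 × 30.44 = 182.6 days | 182.6 + 21 = 203.6 days |
| Month 6, re-treated at month 4, four varnish sessions | 60.9 − 21 = 39.9 days | 60.9 days |
| Month 6, re-treated at month 4, one varnish session | 60.9 days | 60.9 days |
| Month 2, re-treated at month 1, four varnish sessions | 30.4 − 21 = 9.4 days | 30.4 days |
| Month 2, re-treated at month 1, one varnish session | 30.4 days | 30.4 days |

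The resin's unrepeated interval is longer because its only application is on day 0, while follow-up counts from the last simulation.

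**4. Children per arm.** The plan's own figure reproduces first. In a one-way ANOVA with 3 groups, difference 1, SD 0.9 and α = 0.05, the noncentrality is n × 1² / (2 × 0.9²). Power is 0.782 at n = 16 and 0.809 at n = 17. Then 3 × 17 = 51, and 51 × 1.18 = 60.2, the stated 60. So take 17 per arm.

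**5. Scale of a shift in one arm's mean.** If k re-treated children are each lowered by d SCASS points, the arm mean falls by k × d / 17. Both k and d are assumed; the article gives neither.

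| k | d = 1 | d = 2 |
|---|---|---|
| 1 | 0.06 | 0.12 |
| 2 | 0.12 | 0.24 |
| 5 | 0.29 | 0.59 |
| 8 | 0.47 | 0.94 |

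**6. Effect on the contrast.** The planned difference of 1 is between groups, so what counts is the difference between arms in k × d / 17. For example, with 5 children lowered by 1 point in one arm and 2 in another, the contrast moves by (5 − 2) / 17 = 0.18, not 0.29. The single-arm figures are upper bounds, reached only if the comparator arm has no benefit from re-treatment.

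**7. Illustration of masking, on assumed inputs.** Suppose mean SCASS is 0.5 when controlled and 2.0 when relapsed, and relapse after one course is 20% in one arm and 60% in another. If re-treatment restores control in a fraction e of relapsed children, the late difference is (2.0 − 0.5) × (0.60 − 0.20) × (1 − e). This gives 0.60, 0.30, 0.12 and 0 for e = 0, 0.5, 0.8 and 1. With relapse of 20% and 50%, it gives 0.45, 0.225, 0.09 and 0.

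**The case against.** The strongest reply is that nothing is wrong with the analysis. The stated aim is to compare three interventions on sensitivity at set times, and single-course duration is not a formally stated aim. Comparing scores regardless of reapplication is a valid comparison of strategies and can itself address long-term benefit. This stands, and it is why the ANOVA should stay. It does not make those means informative about one course.

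Second, if *maintained* means only that the product is not switched, there is no re-treatment and no dilution. This also stands as a possibility. The two readings lead to different treatment during follow-up, so the sentence needs settling either way.

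Third, a full protocol or analysis plan may already record reapplication. It may. The point rests on what the article does state: an outcome-triggered rule and an analysis that takes the later scores together.

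Fourth, first relapses are visible at the visit that detects them, so poorer durability is partly on show. True, but a child re-treated at one visit may look controlled at the next.

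A reader might go further and infer that re-treatment could erase the planned 1-point difference, pointing to the 0.94 in the table. The article does not support that. The figure needs 8 of 17 children in one arm lowered by 2 points each and no re-treatment benefit in the comparator, and none of these inputs is given. Nor does the Discussion establish reapplication on demand as a rule for all three arms.

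**Conclusion.** The point holds in a limited form, as a cheap improvement. On the more natural reading, relapsed children are re-treated because of their primary outcome and stay in the analysis. The 2-, 4- and 6-month means then describe strategies of treating and re-treating, and alone they do not show whether one course works long term.

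The amount of dilution cannot be computed from the article. What can be given is scale: 0.06 SCASS points in an arm's mean per child lowered by 1 point, with only the between-arm imbalance affecting the contrast. The day counts also rest on a fixed visit calendar, which the article does not settle, because it counts visits from the last application or simulation. If re-treatment restarted that count, the later scores would follow the repeat course, which again says nothing direct about the first.

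It does not follow that the ANOVA is invalid or that the trial cannot address long-term benefit.

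**What to change.** 1. State under Follow-up Examinations that relapse triggers reapplication, if that is the intent, and with how many sessions. The care rule itself need not change.
2. Keep follow-up visits on the calendar fixed from the week-4 session, and take each score before any reapplication.
3. Record the date of each reapplication, and report relapse and reapplication by arm beside the primary result. The entry criterion, under which "a score of 2 or 3 on the Schiff Cold Air Sensitivity Scale (SCASS) will be considered as a positive result", supplies a ready threshold: relapse is a return to 2 or 3 after an earlier 0 or 1. Report children who never reached 0 or 1 separately, as non-response.
4. Keep the planned ANOVA, labelled as the comparison regardless of reapplication.
5. Add one sensitivity analysis that counts a child as a failure from the visit at which reapplication is needed. Success at 6 months is then SCASS 0 or 1 with no earlier reapplication.

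**Cost.** One case-report field and a little more analysis, with no extra visits and no change to care or to the primary analysis. The Results section reports 6 children treated and 1 of them excluded at month 1, so at most 5 are still in follow-up. Their reapplication dates may be incomplete and should be reported as such.

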### Data Analysis

Statistical analysis will be performed with SigmaPlot (version 12.3; SPSS Inc). For the WBFPS, SCASS, and FLACC scale, the three groups and evaluation time will be compared by 2-way repeated measures analysis of variance followed by a Tukey test, based on the recommendation of Cohen [31], to allow for interaction analysis between study factors and to avoid an inflated α error. A Spearman correlation test will be performed to determine if there is a significant correlation among the WBFPS, SCASS, and FLACC scale. The significance level will be set at 5%. Poisson regression will be used to assess the influence of IPV, GI, and discomfort on the outcome. The satisfaction of parents/guardians and participants will be analyzed descriptively.

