### Random Allocation

The included patients will be allocated to one of the 3 treatment options by stratified block randomization: (1) the control group (sodium fluoride varnish; Duraphat, Colgate), (2) experimental group I (4% TiF_4_), and (3) experimental group II (S-PRG resin coating; PRG Barrier Coat, Shofu). The randomization sequence will be generated using Microsoft Excel 365 (Microsoft Corp) by an examiner who will not be involved in any of the clinical trial phases. To ensure allocation concealment, the randomly generated sequence will be sealed in opaque envelopes that will be opened only after the child is ready to receive treatment. The randomization procedure will be done per block of 3 children with the same SCASS scores to guarantee similar scores among groups at baseline.

The analysis unit will be the child and will be considered one tooth per child. If more than one permanent first molar has the condition, all will undergo the same treatment so that there is no interference from different treatments and other factors such as saliva, and one tooth will be selected by a draw to be included in the data analysis. The order of treatment among affected teeth in a patient will also be defined by a draw.

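### Randomisation is blocked on baseline SCASS, but the repeated-measures ANOVA has no baseline term and counts the untreated reading as a time level; 80% power is not established for that test

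*Protocol article*

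**What the plan says.** **Sizing** (Selection of Participants and Sample Size Calculation). The text says "The sample size was calculated considering analysis of variance" and "it was considered a minimally detectable difference of 1 on the SCASS scores between groups". It adds "A standard deviation of 0.9 was used based on a previous study" and "α error was 5%, β error was 20%, and a dropout rate of 18% was used, which resulted in a total of 60 children", that is, 20 per group. It gives no time point, repeated-measures factor or within-child correlation.

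**Randomisation** (Random Allocation). "The randomization procedure will be done per block of 3 children with the same SCASS scores", with the stated aim of making the arms alike at baseline. Entry requires a SCASS of 2 or 3, so there are two strata.

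**Readings** (Primary Outcome). The moments begin with the reading before each application. They continue with the one immediately after application or simulation, then 1, 2, 4 and 6 months after the last session.

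**Analysis** (Data Analysis). For each of the three scales, "the three groups and evaluation time will be compared by 2-way repeated measures analysis of variance followed by a Tukey test". The reason given is "to allow for interaction analysis between study factors and to avoid an inflated α error". The section names no baseline or stratum term, and it does not say whether the group effect, the interaction or a contrast at one visit answers the primary question.

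**The concern.** Three choices fixed in the protocol do not fit together.

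- The design balances the arms on baseline SCASS, but the stated model does not use that variable. Stratification removes between-arm variation that an unadjusted test still counts as error, so the test is too cautious and a real difference is harder to declare.
- If the reading before the first application is a level of time, the group main effect averages the treatment difference with a reading where none can exist.
- The sample size was computed for a simple between-group comparison, and the primary analysis is a different test.

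At stake are lost precision and an unclear primary result. A non-significant group effect could reflect dilution, and choosing between main effect and interaction once the data are seen would be data-driven.

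**Working it through.** **1. Reproducing the 60.** Inputs from the sample size section: difference d = 1, SD = 0.9, α = 5%, power 80%, three arms, dropout 18%. For a one-way ANOVA with two arms d apart and the third midway (the least favourable pattern), the noncentrality is λ = n·d²/(2·SD²) = n/1.62.

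| n per arm | λ | power |
|---|---|---|
| 16 | 9.88 | 78.2% |
| 16.4 | 10.12 | 79.3% |
| 17 | 10.49 | 80.9% |

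So n = 17 per arm, 51 in total, and 51 × 1.18 = 60.2, which matches 60. With 20 enrolled per arm and 18% lost, 20 × 0.82 = 16.4 remain. The sizing is sound for a simple between-group ANOVA.

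**2. Ignoring the stratifier: error rate.** Let r be the correlation between baseline and outcome (not given; assumed 0.3 and 0.5). Stratification shrinks the true between-arm variance by about 1 − r², while the unadjusted error term stays at the full variance. The actual rejection rate under no effect is therefore roughly P(F > F_crit/(1 − r²)). With 2 and 46.2 df, F_crit = 3.199:

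- r = 0.3: 3.199/0.91 = 3.515, giving 3.8%. Simulation gives about 3.7%.
- r = 0.5: 3.199/0.75 = 4.265, giving 2.0%. Simulation gives about 1.8%.

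The repeated-measures group effect goes the same way. With discrete 0 to 3 scores, baseline 2 or 3, 20 per arm and twelve readings, simulated error was 2.5%, 0.6% and 0.4% at within-child correlation 0.3, 0.5 and 0.7.

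**3. Ignoring the stratifier: power.** For a single-time comparison at 16.4 per arm, the adjusted noncentrality is 10.12/(1 − r²), with one df fewer for error:

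- unadjusted: 79.3%
- r = 0.3: λ = 11.12, power 83.1%
- r = 0.5: λ = 13.50, power 89.9%

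**4. Dilution by the untreated reading.** The protocol does not count the readings. I take twelve: four before, four after, four follow-ups. Assume a constant 1-point difference after the first application and a constant within-child correlation ρ. With the baseline reading in, the averaged difference is 11/12 and the variance of a child's mean is 0.81(1 + 11ρ)/12. With it out, these are 1 and 0.81(1 + 10ρ)/11. Noncentrality is n·(difference)²/(2·variance), n = 16.4.

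| ρ | baseline in | baseline out |
|---|---|---|
| 0.3 | 99.2% | 99.7% |
| 0.5 | 94.0% | 97.0% |
| 0.7 | 85.2% | 90.9% |

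The loss is 0.5 to 6 points. If time had only baseline and the four follow-ups, power would be 92%, 82% and 72% with baseline in, against 98%, 95% and 89% with it out.

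**5. Power of the planned test depends on what is unstated.** Simulations used 17 per arm, SD 0.9, arms at 0, −0.5 and −1, twelve readings, and within-child correlation either constant or decaying over time. The interaction was Greenhouse-Geisser corrected.

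| Where the 1-point difference occurs | group effect | interaction |
|---|---|---|
| constant after first application | 93–95% | 37–67% |
| four follow-ups only | 22–23% | 85–99.8% |
| 6 months only | 6–7% | 37–66% |

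In each of the first two patterns one test is strong and the other weak. Which one matters depends on the effect pattern and on the effect chosen to decide, and the protocol fixes neither.

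**The case against.** **Power.** A reader might infer that the trial is underpowered. That inference needs the weaker test to be picked in each row of the last table. A two-way ANOVA yields both a group effect and an interaction, the protocol chose the model in order to examine the interaction, and for a sustained difference one of the two exceeds 80%. A difference confined to 6 months falls short on both in those runs, but nothing in the protocol suggests that pattern. This objection stands: power is undetermined, not shown to be below 80%.

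**Error rate.** A reader might also infer that the 5% level is inflated. Counting baseline as a time level does not do that: the group effect rejected 5% to 6% in null runs without stratification, and omitting the stratifier pushes the rate down. The interaction exceeded 5% (about 11% to 14% unstratified, 6% to 12% stratified) only when correlation decayed over time and no sphericity correction was made. An article commonly leaves that correction to a fuller document, so its absence here is no error.

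**Baseline as a level.** With baseline in the time factor, the interaction tests differential change, which is a legitimate use. Only the reading before the first application is untreated; those before the second to fourth follow treatment. Both points stand, so the dilution argument is confined to the group main effect and to one reading.

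**Paid-for power.** The sizing used the unadjusted SD, so about 79% is what was bought. The gain from adjustment comes on top and rests on assumed correlations with a two-valued baseline. This is fair, but the gain is still free.

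**Conclusion.** The point holds in a limited form. The stated model omits the variable on which randomisation is blocked and, as written, includes the untreated reading among the outcome times. The omission makes the between-arm test conservative (about 3.7% and 1.8% at r = 0.3 and 0.5) and forgoes roughly 4 to 11 points of power at a single time (79% against 83% to 90%). Including the untreated reading costs the group effect a further 0.5 to 6 points if the difference is constant over twelve readings. The 80% belongs to the simple between-group ANOVA, where it reproduces; it does not carry over to the repeated-measures test. These sizes rest on assumed correlations, on treating the scores as continuous except in the discrete check, and on my count of the readings. The documents do not support a claim that power is below 80% or that false positives exceed 5%.

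**What to change.** - Take the pre-treatment reading out of the time factor. Fit a repeated-measures mixed model to the post-treatment readings with arm, visit, arm × visit and baseline SCASS (the stratum) as covariate.
- Name in advance the arm contrast that decides the primary question, with its visit or average of visits. That choice stays with the investigators; no section makes one visit decisive.
- State that the 80% power refers to the simple between-group comparison.
- If the ANOVA is kept, apply a Greenhouse-Geisser correction to the interaction.

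The cost is analysis wording and software that fits the model. No new data or children are needed. The Results section reports only 6 children treated, so the change can be made well before the analysis.

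### Arms are blocked on baseline SCASS, but the planned ANOVA omits that stratum and the baseline scores, so comparisons between arms are somewhat conservative and lose some power

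*Protocol article*

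**What the plan says.** **Design.** Under Random Allocation: "The randomization procedure will be done per block of 3 children with the same SCASS scores to guarantee similar scores among groups at baseline". The selection section admits only children scoring 2 or 3 on the SCASS, so there are two strata.

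**Analysis.** The Data Analysis section says that for WBFPS, SCASS and FLACC "the three groups and evaluation time will be compared by 2-way repeated measures analysis of variance followed by a Tukey test". The factors are group and time. The only other regression named is a Poisson model, whose explanatory variables are plaque index, gingival index and discomfort. No between-arm comparison uses the stratum or a baseline score.

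**Timing.** The Primary Outcome section lists as its first assessment moment the reading "before the application of each material". At week 1 that is the pre-treatment baseline. At weeks 2 to 4 it is already post-baseline.

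**Sample size.** It was based on analysis of variance with a "minimally detectable difference of 1 on the SCASS scores between groups", and "α error was 5%, β error was 20%, and a dropout rate of 18% was used".

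**The concern.** Blocking on a prognostic score makes the arms alike on it, so the arm difference varies less from trial to trial than under simple randomisation. The analysis earns that gain only if the model contains the blocking factor. Otherwise the spread between the SCASS 2 and SCASS 3 children is counted as error, the standard error is too large and the test rejects less often than its nominal 5%.

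WBFPS and FLACC are also primary instruments. Blocking does not balance them directly, and their baselines are collected but not used as covariates. For these scales the issue is mainly lost precision.

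If the reading before the first application is a level of time, the group main effect also averages in an occasion on which no treatment effect can exist.

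What is at stake is efficiency in a trial of 20 children per arm sized for 80% power.

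**Working it through.** **Inputs.** From the article: difference 1 SCASS point, SD 0.9, α 5%, power 80%, dropout 18%, 60 children, entry SCASS 2 or 3. Assumed, because the article does not give them: number analysed per arm, an even split of the strata, arm means 0/0.5/1, and the follow-up difference *d* between strata (or the baseline-to-follow-up correlation ρ).

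**1. The plan's own figure.** One-way ANOVA with three groups has noncentrality nδ²/(2σ²). With n = 17 this is 17 × 1/(2 × 0.81) = 10.49 and power is 0.809; with n = 16 power is 0.782. Then 17 × 1.18 = 20.06, which gives the stated 20 per group and 60 in total. The calculation contains no covariate.

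**2. SCASS at a single visit.** With an even split, the strata contribute variance d²/4. So ρ = (d/2)/0.9, the within-stratum SD is √(0.81 − d²/4), and the unadjusted standard error is too large by 0.9 divided by that SD. Type I error and power come from 20,000 simulated trials per setting (18 per arm, F-test for arm, without and with the stratum).

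| d | ρ | Within-stratum SD | SE factor | Type I error without / with | Power without / with | Gain (points) |
|---|---|---|---|---|---|---|
| 0.25 | 0.14 | 0.891 | 1.01 | 0.045 / 0.048 | 0.830 / 0.836 | 0.6 |
| 0.5 | 0.28 | 0.865 | 1.04 | 0.039 / 0.050 | 0.837 / 0.863 | 2.6 |
| 0.75 | 0.42 | 0.818 | 1.10 | 0.027 / 0.050 | 0.844 / 0.900 | 5.6 |
| 1.0 | 0.56 | 0.748 | 1.20 | 0.013 / 0.049 | 0.856 / 0.945 | 8.9 |

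At zero association adjustment costs essentially nothing: power is 0.809 without and 0.808 with baseline (17 per arm). The single-visit F-test stands in for the Tukey comparison of arms at a visit.

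**3. The repeated measures ANOVA itself.** Further assumptions: 17 per arm, baseline plus nine later readings, correlation 0.6 among the later readings, 4,000 runs. The adjusted column is the test on the post-baseline mean with baseline as covariate; its type I error was 0.048 to 0.053.

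| ρ | Main effect: type I error | Main effect: power | Adjusted post-baseline mean: power | Group-by-time: type I error | Group-by-time: power |
|---|---|---|---|---|---|
| 0 | 0.048 | 0.946 | 0.948 | 0.029 | 0.754 |
| 0.2 | 0.034 | 0.943 | 0.958 | 0.042 | 0.791 |
| 0.4 | 0.015 | 0.956 | 0.986 | 0.044 | 0.840 |
| 0.6 | 0.001 | 0.980 | 1.000 | 0.059 | 0.912 |

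The main effect becomes more conservative as ρ rises. The group-by-time test does not.

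**4. Baseline as a level of time.** With ten levels, one of them baseline, the averaged arm difference is 9/10 of the post-baseline difference. The listed moments give between 4 + 1 + 4 = 9 and 4 + 4 + 4 = 12 levels, depending on whether the immediate reading is taken once or weekly. The factor is then 8/9 = 0.89 to 11/12 = 0.92. The power cost is small: including baseline rather than leaving it out (both unadjusted) gives 0.946 against 0.947, 0.943 against 0.949, 0.956 against 0.968 and 0.980 against 0.989 for the four values of ρ.

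**5. WBFPS and FLACC at a single visit.** Unadjusted variance over baseline-adjusted variance is 1/(1 − r²): 1/0.91 = 1.10 at an assumed r of 0.3 and 1/0.75 = 1.33 at 0.5.

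**The case against.** The strongest reply is that the article names a repeated measures ANOVA chosen to examine interaction, not a single-visit test. In the group-by-time test each child is its own control, so a stratum difference that persists from baseline drops out. A separate simulation of that test (18 per arm, stratum differences 0.25 to 1.0) gave type I error 0.039 to 0.053 and power 0.81 to 0.95. This stands. A reader might infer from the single-visit table that the whole planned analysis is conservative, and that inference is not supported.

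The size also rests on an association the article does not report. A follow-up difference of 1.0 means that none of the 1-point entry difference shrinks after treatment. An even split is also the most favourable case: at *d* = 1 the stratum explains 0.25/0.81 = 31% of variance, against 0.16/0.81 = 20% with an 80/20 split. This stands too, so the last rows of the table are an upper end.

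Unadjusted power at 18 per arm is 83% to 86%, above the 80% target. That is correct, but it depends on 18 completers. At the planned 18% dropout, 60 × 0.82 = 49.2 children remain, about 16 per arm, where the plan's own formula gives 0.782. There is little power to spare.

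Keeping baseline as a response level is a legitimate longitudinal choice, and the article does not list the levels of time. Baseline as a level is the natural reading of two sections together, not an explicit statement, and it cannot be called an error in itself.

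Finally, a fuller analysis plan may exist. But the article itself fixes the model, its factors, the post-hoc test and the software, so the mismatch with the randomisation is on the page.

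**Conclusion.** The point holds as a matter of efficiency. For SCASS, the planned group main effect and arm comparisons at a visit leave out the factor on which allocation was blocked, so their standard errors are too large whenever that factor predicts outcome. Single-visit power loss is nil at no association, about 1 to 3 points for stratum differences of 0.25 to 0.5, and about 6 to 9 points at 0.75 to 1.0, given 18 per arm, SD 0.9 and evenly split strata. If baseline is a level of time, the averaged group effect also shrinks by about a tenth, with little further loss of power.

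Three stronger readings go beyond the documents. Omitting the stratum does not bias the comparison of arms at a visit. It makes those between-arm tests conservative, so it does not inflate false positives. Nor can one say that it takes the trial below its planned power, because the association is unknown and the sample size never counted on a covariate.

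**What to change.** In the Data Analysis section, make the between-arm comparison on post-baseline readings only. Include the SCASS randomisation stratum (2 or 3) as a factor for all three scales. For WBFPS and FLACC, add the scale's own score before the first application as a covariate. Define baseline as that reading, so that the pre-application readings of weeks 2 to 4 count as post-baseline. Report adjusted arm differences with 95% confidence intervals, and keep the before-and-after comparison within groups as a descriptive summary.

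The cost is one or two degrees of freedom, a sentence or two of wording, and software that fits a covariate in a repeated-measures model; whether the named package does so should be checked. No new data or additional children are needed. The article reports six children treated, so at that stage the change could be made before comparative results were known.
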